
### Sample size calculation

The sample size calculation was performed to compare the improvement in disability (eg, changes in ODI scores) from baseline to 16 weeks between MC+ILEX and free-weight resistance training exercise groups. This calculation was conducted using PASS 2023 software for two-sample t-test based on effect size. The minimum required sample size is 90 (45 per group) to detect a standardised effect size of 0.60 (Cohen’s d effect size), with 80% statistical power at the significance level of 0.05 (two-sided test), assuming an equal variance within the low (LSIQ<9) and high (LSIQ≥9) instability strata.^21^ Cohen’s d effect size of 0.60 falls within the range considered as a medium effect.^100^ This effect size is a conservative choice for the sample size calculation, given that the estimated Cohen’s d is approximately 0.79 based on the disability improvement observed in the MC+ILEX group from our previous work^35^ (mean=9.7, SD=10) and the disability improvement reported by Welch *et al*^34^ for the free-weight resistance training exercise group (mean=17.5, SD=5). A total of 106 participants (53 per group) will be recruited to account for a 15% loss to follow-up.^35 101^

### Statistical analysis

For the primary outcome, we will employ linear mixed-effects model for repeated measures over time using ODI as the dependent variable. The model will include effects for group (MC+ILEX vs free-weight resistance training), time (baseline vs 16 weeks) and group by time interaction. LSIQ score (high >9 and low ≤9) will be incorporated as a covariate and an unstructured covariance matrix will be used. Within the mixed model, we will calculate 95% CIs and p values for the two group contrasts, and for changes in ODI score within each group over 16 weeks. We will conduct similar analyses focusing on multifidus muscle composition and lumbar extensor muscle strength as separate dependent variables. To investigate if changes in multifidus muscle composition mediate improvements in disability, path analysis will be conducted to test the following paths: (a) group allocation at baseline (independent variable) → changes in multifidus muscle composition from baseline to 16 weeks (mediator); (b) changes in multifidus muscle composition from baseline to 16 weeks → changes in disability score (eg, ODI) from baseline to 16 weeks (dependent variable); and (c) group allocation at baseline → changes in disability score from baseline to 16 weeks. LSIQ score (high >9 and low ≤9) will be included in the model as an exogenous variable. For paths (b) and (c), disability score at baseline will be included as exogenous variables as well. The direct, indirect and total effects of treatment on the change in multifidus muscle composition and its 95% CI will be calculated based on non-parametric bootstrap. In addition, the mediation percentage is defined as the ratio of the indirect effect to the total effect, thereby quantifying the size of the mediation effect. The significance of the mediation effect will be tested using bootstrap sampling (times=1000). The model fit will be assessed using the following model fit indices: comparative fit index, Tucker-Lewis index and root mean square error of approximation.^102^ To explore if baseline score on the LSIQ can moderate the response to exercise training in chronic LBP at 16 weeks, we will conduct a linear regression model with changes in multifidus muscle composition from baseline to 16 weeks as the dependent variable. The independent variables will include group, LSIQ score (high >9 and low ≤9) and the interaction between group and LSIQ score (high >9 and low ≤9). Multifidus muscle composition at baseline will be adjusted as covariates in the model. Similar analyses will be conducted with changes in ODI score, multifidus size, lumbar extensor strength, pain, sleep and quality of life score from baseline to 16 weeks as the dependent variables, separately. Both complete case analysis and multiple imputation will be conducted to handle missing data. Any participant characteristics identified to be associated with missingness and the outcome will be integrated into the multiple imputation process. This will be accomplished using the fully conditional specification method fitted using predictive mean matching approach. Given the potential for missing data that are not missing at random, we will perform a sensitivity analysis to assess the robustness of our findings under the most unfavourable assumptions about the missing data. In this analysis, if we show that the MC+ILEX group is more effective than the free-weight resistance training exercise group in improving patients’ disability, all missing outcomes at 16 weeks will be imputed with the worst observed outcome in the MC+ILEX group and the best observed outcome in the free-weight resistance training exercise group, and vice versa.

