**Methods and analysis:**

A total of 106 participants will be recruited through primary and secondary care and randomised (1:1) to receive either MC+ILEX or free-weight resistance training. Both groups will complete 48 exercise sessions over 16 weeks. The primary outcome will be disability at 16 weeks, measured by the Oswestry Disability Index. Secondary outcomes include multifidus muscle composition and size, lumbar and gluteal muscle strength, hip range of motion, pain, physical and mental function, satisfaction and recovery, health-related quality of life, sleep quality and physical activity levels. Linear mixed-effects models will be used to assess primary and secondary outcomes. Regression analyses will explore whether baseline LSIQ scores moderate treatment effects on multifidus composition and other outcomes. A subsample of participants will undergo semistructured interviews before and after the intervention to explore their illness perceptions, illness mindsets, perceptions of exercise therapy, as well as their experiences and satisfaction with the two exercise interventions. Reflexive thematic analysis will be used to analyse qualitative data.

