### Data collection

All paraspinal muscle health-related outcomes will be collected in person at the School of Health (Concordia University). Self-reported questionnaire outcomes will occur preferentially using ‘*Manage My Pain*’ at appropriate intervals to the participants. Alternatively, if needed in French, self-reported measures may be answered over the phone or done in person using paper copies based on participants’ preference. Sleep quality will be collected at home using an actigraphy watch, as described below. All outcomes (primary and secondary) will be assessed at baseline and 16 weeks (end of the intervention) in both groups. Pain ratings will also be collected weekly throughout the entire intervention using a mobile app (refer to secondary outcomes). All the questionnaires will be administered via the clinically validated digital health application ‘*Manage My Pain’* by ManagingLife.^64^ Manage My Pain is a clinically validated app-based solution that helps people with chronic pain self-manage and better engage their care team. For clinicians and researchers, it facilitates a more effective way to measure outcomes along the patient journey.

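### The primary mixed model leaves baseline ODI free by arm, so its group-by-time test is in effect an unadjusted change-score comparison: valid, but less precise than the data allow, with the primary contrast not named

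*Protocol article*

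**What the plan says.** All from the protocol article.

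- **Model (Statistical analysis).** ODI is a repeated outcome: "we will employ linear mixed-effects model for repeated measures over time using ODI as the dependent variable". The fixed effects are group, time and their interaction: "The model will include effects for group (MC+ILEX vs free-weight resistance training), time (baseline vs 16 weeks) and group by time interaction". The stratification factor and covariance follow: "LSIQ score (high >9 and low ≤9) will be incorporated as a covariate and an unstructured covariance matrix will be used".
- **Time points (Data collection).** There are two: "All outcomes (primary and secondary) will be assessed at baseline and 16 weeks (end of the intervention) in both groups".
- **Contrasts (Statistical analysis).** "we will calculate 95% CIs and p values for the two group contrasts, and for changes in ODI score within each group over 16 weeks". The between-group contrasts are not defined further.
- **Endpoint wording.** The abstract says "The primary outcome will be disability at 16 weeks, measured by the Oswestry Disability Index". The sample size section instead sets out to "compare the improvement in disability (eg, changes in ODI scores) from baseline to 16 weeks".
- **Elsewhere in Statistical analysis.** The mediation model enters baseline disability as an exogenous variable on paths (b) and (c), so ODI change is adjusted for baseline there. Similar mixed models are planned for multifidus composition and lumbar extensor strength.

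**The concern.** Baseline ODI is modelled as an outcome whose mean may differ by arm, although randomisation makes the two arms' baseline means equal in expectation. With only two time points and an unstructured covariance, the group-by-time term then reduces to the difference in mean change. That estimator subtracts the whole baseline value instead of regressing on it, so it carries avoidable noise and stays sensitive to chance baseline imbalance.

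The same model also yields a 16-week group difference, which is not adjusted for baseline ODI either. The abstract's wording fits that contrast, and the sample size wording fits the change contrast. The two have the same expectation under randomisation, but they differ in precision and in response to chance imbalance, so in one dataset they can give different p values. With 90 evaluable participants planned, both the lost precision and the open choice of contrast matter.

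**Working it through.** **1. The plan's own figure.** Inputs from Sample size calculation: d = 0.60 on ODI change, two-sided 0.05, 80% power, two-sample t-test, 15% loss. The noncentral t gives power 0.795 at 44 per arm and 0.804 at 45, so 45 per arm (90) is reproduced. Inflation: 90/0.85 = 105.9, so 106. The plan is consistent with an unadjusted change-score test.

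**2. What the stated model tests.** The model was fitted by REML to four simulated complete trials of 106 participants (assumed r = 0.5), with LSIQ stratum made to predict both baseline and change. The group-by-time estimate and SE matched the raw difference in mean change and its pooled t-test SE to five decimals (for example 1.57051, SE 2.30769). They were the same with or without the LSIQ main effect.

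With 15% of 16-week values missing (200 simulated trials per r), the match is close but not exact. The correlation between the two estimates was 0.975 to 0.985 for r = 0.3 to 0.7.

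**3. Variance and power at 45 per arm.** Let r be the correlation between baseline and 16-week ODI, which the protocol does not give, and let the SD be σ at both times (assumed). Per-participant variances are:

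- change score: 2σ²(1 − r)
- raw 16-week value: σ²
- 16-week value adjusted for baseline: σ²(1 − r²)

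The ratio of adjusted to change is (1 − r²)/[2(1 − r)] = (1 + r)/2. Holding the true effect at 0.60 change-score SDs, the standardised effect becomes 0.60/√[(1 + r)/2] for the adjusted contrast and 0.60·√[2(1 − r)] for the raw 16-week contrast.

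| r | Variance ratio, adjusted/change | Power, change | d adjusted | Power, adjusted | d raw 16-week | Power, raw 16-week |
|---|---|---|---|---|---|---|
| 0.4 | 0.70 | 80% | 0.717 | 92% | 0.657 | 87% |
| 0.5 | 0.75 | 80% | 0.693 | 90% | 0.600 | 80% |
| 0.6 | 0.80 | 80% | 0.671 | 88% | 0.537 | 71% |
| 0.7 | 0.85 | 80% | 0.651 | 86% | 0.465 | 59% |

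At r = 0.9 the ratio is 0.95, the SE falls by only 2.5%, and adjusted power is 82%.

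**4. Counting dropouts' baselines.** The mixed model also uses baselines from participants lost to follow-up. With 53 baselines and 45 completers per arm, the variance per arm (in units of σ²) is (1 − r²)/45 + (1 − r)²/53 for the planned model and (1 − r²)/45 for the common-baseline model.

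- r = 0.4: 0.84/45 + 0.36/53 = 0.01867 + 0.00679 = 0.02546; ratio 0.01867/0.02546 = 0.73.
- r = 0.7: 0.51/45 + 0.09/53 = 0.01133 + 0.00170 = 0.01303; ratio 0.01133/0.01303 = 0.87.

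Planned-model power becomes about 81% to 82%; adjusted power stays at 86% to 92%.

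**5. Simulation with 15% loss.** Empirical SD of the estimate, planned model against common-baseline model with LSIQ-by-time: 3.00 against 2.51 (r = 0.3), 2.51 against 2.17 (r = 0.5), 1.86 against 1.78 (r = 0.7).

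**6. How much of this is LSIQ.** Little. Adding only LSIQ-by-time to the planned model moved the SE by less than 1% in the four complete-data trials. In a separate simulation (r = 0.6, LSIQ related to change) the SD fell from 0.180 to 0.175, about 3%. Most of the gain comes from baseline ODI.

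**The case against.** The strongest reply is that nothing here is an error. The group-by-time test is unbiased under randomisation, and the sample size was built on the same comparison, so the trial delivers the power it states. That stands: this is a point about efficiency and clarity, not validity.

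On the contrast, the abstract may only be naming the outcome and its time, and "we will calculate 95% CIs and p values for the two group contrasts" may simply mean the comparison of the two arms. The primary aim, the sample size and the interaction term all sit comfortably with the change contrast. This is a fair reading, but the text does not settle it, and the table shows that the choice affects power.

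The gain also depends on an unstated correlation and on equal SDs, and it shrinks as the correlation rises. That too stands. It is why a range is shown.

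Two stronger readings are tempting and are not supported:

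- A reader might infer that the primary test ignores the stratification factor. That requires taking the LSIQ covariate as a main effect only. An article need not list every interaction, a fuller plan may include LSIQ-by-time, and the effect on the SE is about 3% or less either way.
- A reader might infer that the moderator regressions, which adjust for the baseline value of the outcome, give a second overall treatment effect on ODI. They include a group-by-LSIQ interaction, so their group coefficient is specific to a stratum. The baseline-adjusted ODI comparison in the protocol is in the mediation model, which is a secondary, mechanistic analysis.

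**Conclusion.** The point holds as one of precision and specification. As written, the primary group-by-time test is an unadjusted change-score comparison, exactly on complete data and approximately with 15% loss. It is valid and meets its stated power.

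For an assumed correlation of 0.4 to 0.7 and equal SDs at both times, conditioning on baseline ODI would cut the variance to about 70–85% of the planned value (73–87% with dropouts' baselines counted). Power would rise from about 80–82% to about 86–92%. At a correlation of 0.9 the gain is negligible.

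Separately, the primary contrast is not named. Under the same assumptions, testing the model's raw 16-week difference would fall below 80% power once the correlation exceeds 0.5. The protocol already conditions on baseline disability in the mediation paths, so adjusting the primary analysis would also bring the two into line.

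**What to change.** Replace the primary model with one of these:

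- the mixed model with a common baseline mean: time, group-by-time, LSIQ stratum and LSIQ-by-time, with no group main effect and an unstructured covariance; or
- ANCOVA of 16-week ODI on group, baseline ODI and LSIQ stratum, with the planned multiple imputation for missing follow-up.

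The two agree closely when follow-up is complete. With missing data the agreement is only approximate: the mixed model keeps the baselines of those lost, whereas ANCOVA needs the imputation to retain those participants. One should therefore be chosen as primary. The LSIQ-by-time term is a minor addition.

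Name the baseline-adjusted group difference in ODI at 16 weeks as the single primary contrast, and use the same model for %FSF and lumbar extensor strength. With baseline conditioned on, the 16-week and change contrasts coincide, which removes the ambiguity.

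The cost is a change of wording in the protocol and analysis plan, best made before outcome data are seen. Data, software and the recruitment target of 106 are unaffected.

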Patients with predominant nociceptive chronic LBP have structural changes in the paraspinal muscles, particularly the multifidus.^13 27^ Increased multifidus fatty infiltration is associated with higher pain severity, dysfunction, reduced strength, impaired voluntary contraction and poorer surgical outcomes.^28^,^30^ Fatty infiltration also reflects diminished muscle quality and metabolic resilience and is a recognised marker of sarcopenia.^31 32^ Accordingly, a large body of evidence supports the justification for considering paraspinal muscle dysfunction as a pillar component of rehabilitation programmes for LBP.^13^ Although exercises such as MC, isolated lumbar strengthening exercise and free-weight resistance training are promising forms of exercises for improving paraspinal muscle quality and function,^33^,^35^ most trials focused on patient-reported outcomes rather than structural muscle changes.^36^ Current recommendations from clinicians and evidence from systematic reviews reflect ongoing uncertainty about the specific mechanisms through which exercise improves pain and disability in chronic LBP. While it is widely believed that improving paraspinal muscle quality leads to better outcomes, this hypothesis remains largely unexplored, and a key question remains: *Does improvement in paraspinal muscle composition mediate changes in clinical outcomes in patients with predominant nociceptive chronic LBP?* Linking therapeutic outcomes to underlying mechanisms is essential to guide the clinical decision-making process. The approaches proposed in this study aim to address this gap, improve the effectiveness of commonly available interventions and advance precision rehabilitation.

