### Objectives

Our primary aim is to determine which 16-week exercise intervention, namely motor control plus isolated lumbar extension exercises (MC+ILEX, arm 1) or free-weight resistance training (arm 2), is more effective in improving disability in patients with predominant nociceptive chronic LBP. Secondary aims are to (1) assess whether changes in multifidus muscle composition mediate improvements in disability; (2) compare the effects of both interventions on multifidus size and quality, lumbar extensor and gluteal strength, hip range of motion (ROM), pain, health-related quality of life, sleep quality, physical activity level, and satisfaction and recovery; (3) explore whether baseline scores on the Lumbar Spinal Instability Questionnaire (LSIQ) and sex/gender act as moderators of treatment response at 16 weeks; and (4) explore participants’ perceptions, mindsets, experience and satisfaction of exercise therapy before and after completing the 16-week interventions.

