#### Free-weight resistance training (control arm)

Free-weight resistance training, or compound exercise, is also among the most used forms of exercise therapy for chronic LBP, with systematic reviews documenting its effectiveness.^4 51^ The primary goal of resistance training in LBP is to address impairments in muscle strength, muscle quality and endurance.^57 58^ As previously mentioned, this intervention will be a replication of a previous study conducted by Welch *et al,*^34^ which reported a significant decrease in intramuscular fatty infiltration following a progressive 16-week free-weight resistance programme (without an ILEX component). The exercises will be delivered across two sessions. Session 1 will include the warm-up as prescribed by Welch *et al*,^34^ with minor regressions as needed (described below), followed by: isometric glute raise progressing to single-leg glute raise; mini squat to chair progressing to goblet squats; isometric split-squat hold progressing to split squats; planks on knees progressing to planks on toes; and neutral-grip machine row progressing to standing over-row. Session 2 will include a standardised warm-up (gluteus myofascial release; pelvis tilt as a regression for glute raise; multidirection weight transfer progressing to multidirection lunges; knee pulls followed by supine straight-leg raise as a regression for standing hamstring stretch; overhead squat; and assisted squat using long-loop resistance bands instead of the Smith machine), followed by: short hip hinge progressing to deadlift; step-ups; lat pulldown; side bridge on knees progressing to side bridge; and press-up on knees progressing to press-up on toes.^34^ Sessions will alternate weekly: two Session 1 and one Session 2 in 1 week, then one Session 1 and two Session 2 in the following week.^34^ During the first 4 weeks, participants will complete three sets of each exercise and the load will be set at 10RM. Starting at week 5, participants will complete three sets of five repetitions and the load will be set at 6–7RM. Participants who are unable to perform deadlifting off the floor (eg, limited lumbar flexion) will have the bar raised to a level in a squat rack, where a straight back can be maintained. Due to the need to learn new techniques/skills involving the coordination of movement and free weights (eg, force is not in a fixed plane like in a resistance machine),^62^ participants will be filmed when completing their exercises with coaching cues to maximise skill acquisition and learning.^63^

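### The mediation aim asks about improvement in disability, but the declared test and mediation percentage address only the difference between two active programmes

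*Protocol article*

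**What the plan says.** The Introduction poses the key question: "Does improvement in paraspinal muscle composition mediate changes in clinical outcomes in patients with predominant nociceptive chronic LBP". Secondary aim 1 in Objectives is to "assess whether changes in multifidus muscle composition mediate improvements in disability". Both concern improvement, not a difference between programmes.

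The Statistical analysis section states: "To investigate if changes in multifidus muscle composition mediate improvements in disability, path analysis will be conducted to test the following paths". It sets out three paths:
- Path (a) is "group allocation at baseline (independent variable) → changes in multifidus muscle composition from baseline to 16 weeks (mediator".
- Path (b) runs from multifidus change to ODI change.
- Path (c) runs from arm to ODI change.

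LSIQ stratum is an exogenous variable, and baseline ODI is added for paths (b) and (c). Direct, indirect and total effects are described as effects of treatment. For size, "the mediation percentage is defined as the ratio of the indirect effect to the total effect", with no condition on when it is reported. Significance of mediation is tested with 1,000 bootstrap samples.

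There is no non-exercise arm. The Introduction names motor control, isolated lumbar strengthening and free-weight training as promising for paraspinal muscle quality. The MC+ILEX section expects morphological adaptation. The free-weight section replicates a study "which reported a significant decrease in intramuscular fatty infiltration following a progressive 16-week free-weight resistance programme".

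**The concern.** With arm as the exposure, mediation here means that one programme changes multifidus more than the other and that this explains its advantage in ODI. That is a narrower question than the one in the aim. Both programmes were chosen partly because they should reduce fat infiltration, so a small arm difference in %FSF change is plausible. The Introduction also says that differences between exercise approaches remain modest, so a small total effect, which is the denominator of the percentage, is plausible too.

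At stake is the interpretation of a mechanistic aim that appears in the abstract, Objectives and Discussion and is meant to inform clinical decisions. With aim 1 worded as it is, a null indirect effect could be taken to count against the mechanism when it shows only that the two programmes did not separate on the mediator.

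**Working it through.** **Plan's own figure.** The only stated sample size is for the primary comparison. For d = 0.60, 80% power and two-sided 0.05, the exact two-sample t-test needs 44.6, so 45 per arm (power 0.804). Then 90 / 0.85 = 105.9, so 106. The plan's figures reproduce. No figure is given for the mediation analysis.

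**Algebra.** Let a be the arm difference in %FSF change, b the slope of ODI change on %FSF change within arm, and c′ the direct effect.
- Indirect effect = a × b
- Total effect = a × b + c′
- Mediation percentage = a × b / (a × b + c′)

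If a = 0, the indirect effect is 0 for any b. If c′ is also 0, the percentage is 0/0.

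**Simulation 1: full mediation.** Inputs from the protocol are 45 completers per arm and a 1,000-sample bootstrap (percentile intervals). Assumed inputs: both arms improve %FSF by at least 1 SD; c′ = 0; standardised b = 0.5, 0.7 or 0.9; arm difference in %FSF change of 0 to 0.6 SD; no confounding of path (b). There were 500 trials per setting. The last two columns give the central 95% range of the estimated percentage.

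| Arm difference (SD) | Indirect effect significant | Path (b) significant | Percentage, b = 0.5 | Percentage, b = 0.9 |
|---|---|---|---|---|
| 0 | 4–8% | 100% | −612% to 401% | −354% to 635% |
| 0.2 | 17% | 100% | −767% to 650% | −291% to 409% |
| 0.4 | 48–52% | 100% | −472% to 1141% | 1% to 238% |
| 0.6 | 80–83% | 99–100% | −699% to 772% | 68% to 190% |

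In every row, change in ODI within each arm depends on the person's %FSF change with the same slope. Only the separation between arms varies, and it drives the declared test. The percentage settles only when the total effect is sizeable: at 0.6 SD it is 0.5 × 0.6 = 0.30 SD for b = 0.5, and 0.9 × 0.6 = 0.54 SD for b = 0.9.

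The share of estimates outside 0–100% is a poor summary here. Under full mediation the true value sits at the boundary (median estimate 100% for b = 0.9 at 0.6 SD), so about half exceed 100% even when estimation is good. The width of the range is the relevant figure.

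**Simulation 2: the plan's effect size with partial mediation.** Assumed a = 0.5 SD and b = 0.36, with a total effect of 0.60 SD. The true percentage is 0.5 × 0.36 / 0.60 = 30%. With 90 completers and 5,000 trials, the estimate had median 29% and a central 95% range of 5% to 87%. Repeat runs put the upper end at 88% to 91%.

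**The case against.** A reader might infer that the key question is left unanswered, or that the mediation analysis is invalid. The protocol supports neither.

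- **Path (b) is planned.** It is one of the paths to be tested, in a model with arm, LSIQ stratum and baseline ODI, and that is most of the regression needed. This stands. The mismatch lies in the declared test and the percentage, not in every coefficient.
- **Mediation of a randomised contrast is a legitimate target.** This stands. When a = 0, an interval that includes zero in about 95% of trials is nominal coverage, so the 4–8% in the first row is correct behaviour for the narrower question.
- **Equal arms are not what the plan expects.** It designs for d = 0.60 and cites an estimate of about 0.79. This bears on the total effect but not on path (a), for which no expected value is given. It does make a near-zero denominator less likely, though Simulation 2 shows wide imprecision even at d = 0.60.
- **Misreading of a null is a prediction.** This stands. Nothing in the protocol says a null would be reported as evidence against the mechanism, and the within-arm changes in ODI and multifidus composition would be reported alongside.
- **Path (b) is weaker evidence.** It is a non-randomised association between changes over the same 16 weeks, with outcomes measured only at baseline and the end, so it cannot establish direction. This stands and belongs in the fix.
- **Reporting rules for a ratio can be left to an analysis plan.** This stands in part. The article does fix the percentage, without condition, as the measure of the size of mediation.

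**Conclusion.** The point holds as a mismatch between aim and estimand. Aim 1 and the key question concern mediation of improvement, whereas the declared test and percentage concern mediation of the between-arm difference. The consequence is conditional. Under full mediation with 45 per arm, the chance of a significant indirect effect runs from 4–8% with no arm difference in %FSF change to 80–83% at 0.6 SD, and the protocol does not say where in that range the trial should fall. The percentage is uninformative when the total effect is small and imprecise even at the planned d = 0.60 (about 5% to 87% for a true 30%). These figures rest on the assumed slopes, arm differences and absence of confounding; the algebra does not. The primary outcome, the sample size and data collection are unaffected.

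**What to change.** 1. Reword secondary aim 1 as whether multifidus change mediates the between-arm difference in ODI change.
2. Name the already planned path (b) as the analysis that addresses the Introduction's key question. Add baseline %FSF to its covariates, as the moderation model for multifidus composition already does. Label it associational, and note that concurrent changes do not establish direction.
3. State that a null indirect effect does not exclude the mechanism, because two programmes with similar effects on %FSF would produce it.
4. Report the mediation percentage only when the CI of the total effect excludes zero, and give it its own CI.

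The cost is wording and one regression on data already being collected. The downside is a more modest mechanistic claim.

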### Baseline assessment

Sociodemographic characteristics will be acquired via the Canadian minimum dataset self-reported questionnaire at baseline, after randomisation.^65^

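### The mediation model adjusts the multifidus-to-disability path only for LSIQ class and baseline ODI, so shared causes can bias that path and, if the arms differ in multifidus change, the indirect effect

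*Protocol article*

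**What the plan says.** Secondary aim 1 in the Objectives is to "assess whether changes in multifidus muscle composition mediate improvements in disability". The Statistical analysis section sets out a path model with three paths. Path (a) runs from randomised group to "changes in multifidus muscle composition from baseline to 16 weeks (mediator"). Path (b) is ("b) changes in multifidus muscle composition from baseline to 16 weeks → changes in disability score (eg, ODI) from baseline to 16 weeks (dependent variable"). Path (c) is ("c) group allocation at baseline → changes in disability score from baseline to 16 weeks").

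The covariates are stated. For the whole model, "LSIQ score (high >9 and low ≤9) will be included in the model as an exogenous variable". In addition, "For paths (b) and (c), disability score at baseline will be included as exogenous variables as well". Nothing else is listed. The indirect effect and its ratio to the total effect are to be estimated with a 1000-sample bootstrap, and fit is to be judged by CFI, TLI and RMSEA.

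For the moderation regression the same section does adjust for the baseline value of the muscle measure: "Multifidus muscle composition at baseline will be adjusted as covariates in the model".

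Other candidate covariates will be available. Under Baseline assessment, "Sociodemographic characteristics will be acquired via the Canadian minimum dataset self-reported questionnaire at baseline". The Data collection section has all primary and secondary outcomes measured at baseline, which includes pain and the IPAQ. Age is needed for eligibility, and sex for the moderator aim.

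**The concern.** Randomisation makes group independent of everything measured before it, so path (a) and the total effect need no further adjustment to be unbiased. It does nothing for path (b). Nobody is allocated to a given amount of multifidus change, so within an arm the association of muscle change with ODI change is observational. Any variable that drives both changes is absorbed into the path (b) coefficient and multiplied into the indirect effect.

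The other tools in the plan do not pick this up. The bootstrap measures sampling error. As the model is written, group and LSIQ enter both equations, and the one evident restriction is that baseline ODI has no arrow to the mediator. The fit indices therefore test little more than that restriction, and a confounded path (b) can sit inside a model that fits perfectly. The stated sensitivity analysis concerns missing data.

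At stake is the mechanistic question that the Introduction puts at the centre of the trial, and the planned ratio of indirect to total effect. The primary comparison is not at stake.

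**Working it through.** **Inputs from the protocol.** 45 per group, 90 evaluable; standardised effect 0.60; 80% power; two-sided 0.05; 15% loss; 106 recruited (Sample size calculation). The equations are as quoted above.

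**The plan's own figure.** An exact two-sample t calculation at 0.60 SD with 45 per group gives power 0.804, and 90 / 0.85 = 105.9, so 106. Both reproduce. The protocol gives no figure for the mediation analysis.

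**Assumptions, none of them in the protocol.** Standardised units; true effect of the mediator on the outcome b = 0; one omitted cause U, independent of group, LSIQ and baseline ODI, with the same loading r on both changes; arm effect a on the mediator of 0, 0.3 or 0.6 SD.

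**Bias in path (b).** Given group, the variance of the mediator change is r² + (1 − r²) = 1, and its covariance with the ODI change through U is r × r. The fitted coefficient therefore centres on r² instead of 0:
- r = 0.2: 0.04
- r = 0.3: 0.09
- r = 0.5: 0.25

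Simulated means were within about 0.01 of these values (for example 0.086 and 0.257 for r = 0.3 and 0.5 at a = 0.6). The false indirect effect centres on a × r². For a = 0.6 and r = 0.5 this is 0.6 × 0.25 = 0.15 (simulated 0.156).

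**How often it is declared significant.** The bootstrap interval for the product excludes zero roughly when both coefficients are clear of zero, so the rate is about P(a significant) × P(b significant).
- SE of a = √(2/45) = 0.211. P(a significant) = 0.05, 0.296 and 0.812 for a = 0, 0.3 and 0.6.
- SE of b = √(1 − r⁴) / √85 = 0.108, 0.108 and 0.105 for r = 0.2, 0.3 and 0.5, where 85 = 90 − 5 coefficients. P(b significant) = 0.066, 0.133 and 0.663.

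Products, with simulated rates in brackets (protocol covariates, percentile bootstrap):

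| Arm effect on mediator | r = 0.2 | r = 0.3 | r = 0.5 |
|---|---|---|---|
| 0 | 0.3% (0%) | 0.7% (0.5%) | 3.3% (3–4%) |
| 0.3 SD | 2.0% (0.3–2%) | 3.9% (about 5%) | 19.6% (17–21%) |
| 0.6 SD | 5.3% (5–6%) | 10.8% (9–12%) | 53.8% (52–54%) |

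The bracketed ranges cover repeat runs of 400 to 600 trials. With 600 trials the Monte Carlo standard error is about 1 point near 5–10% and 2 points near 50%. One further run of 800 trials gave 7% in the cell for 0.6 SD and r = 0.2.

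**With U in both equations** (a = 0.6, r = 0.5), the mean b is 0.01, the mean indirect effect 0.004 and the rejection rate 5.2%.

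**The case against.** The strongest reply is that the alarming figures need two things at once, and the documents establish neither. First, the arms must truly differ in multifidus change. The protocol gives no effect size for the multifidus; its 0.60 belongs to the ODI. Both arms were chosen partly because they are expected to improve paraspinal muscle, so a small difference is at least as plausible as a large one. Second, the confounding must be strong: a loading of 0.5 means one factor explains about a quarter of the variance (0.5² = 0.25) of both changes, beyond LSIQ and baseline ODI. The Introduction links the level of fatty infiltration to pain and dysfunction, which is not evidence about change. Opposite-sign loadings would hide mediation instead. This objection stands as to size, and it is why the table starts at a zero arm effect and a loading of 0.2.

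It is also fair that part of the problem is already handled. The ODI includes pain content, so adjusting for its baseline value covers some of baseline pain. Eligibility narrows comorbidity, cognitive-emotional drivers and recent intensive trunk training. Age from 18 to 60, sex and general activity remain free to vary.

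A condensed article may leave a sensitivity analysis for unmeasured confounding to an analysis plan, so its absence here is not counted as a fault. The covariate list is different, because the protocol states it.

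A reader might go further and infer that a significant indirect effect would probably be an artefact, or that the authors will report association as proven mechanism. The first needs confounder strengths and an arm effect that appear nowhere in the documents; the second predicts wording that no section contains.

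**Conclusion.** The point holds as a weakness of a stated model for a secondary aim. Path (b) is adjusted only for LSIQ class and baseline ODI. Any further shared cause of the two changes biases it, by about 0.04 to 0.26 standardised units under the loadings assumed here, even when the arms do not differ in muscle change. The indirect effect inherits the bias only in so far as the arms do differ. Its false-positive rate then runs from below nominal (no arm effect, or 0.3 SD with weak confounding) to about half of trials (0.6 SD with strong confounding). These rates rest on a single confounder with equal, same-sign loadings, 90 evaluable participants and a true b of zero. The real size and direction cannot be derived from the documents. The primary ODI comparison, path (a), the total effect and the sample size are unaffected.

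**What to change.** In the mediation part of the Statistical analysis section, add baseline age, sex, pain, physical activity and multifidus composition to both the mediator and the outcome equation. Use the same summary of multifidus composition that defines the mediator; the moderation model already adjusts for its baseline value. The protocol places the sociodemographic questionnaire after randomisation, which does no harm for age and sex.

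Measured covariates cannot remove all confounding: the return to about 5% in the simulation assumes that the shared cause is measured without error. So also report the residual correlation between mediator and outcome at which the indirect effect becomes zero. In the set-up above, loadings of 0.2, 0.3 and 0.5 correspond to residual correlations of r² = 0.04, 0.09 and 0.25, which gives readers a scale.

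The cost is small and needs no new data. With five single-coefficient terms and 90 participants, residual degrees of freedom fall from 87 to 82 in the mediator equation (90 − 3, then − 5) and from 85 to 80 in the outcome equation (90 − 5, then − 5). There is one extra analysis to report. The list should be fixed before outcome data are examined by arm, so that covariate choice cannot follow the result.
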